### Outcome Variables

#### Research Question 1 (Primary and Secondary Outcome Variables)

Stress, anxiety, and pain represent the primary outcome variables that will be measured using paper-and-pencil questionnaires.

The secondary outcome variables were overall quality of life, emotional status, mental well-being, self-efficacy perception, and patient activation during and after hospital stay.

To assess the primary outcome variables, the following questionnaires will be used after each standard care visit and will be administered by paper and pencil:

Patients’ and caregivers’ *self-reported stress* was measured using a VAS at enrollment (baseline), at admission for surgery, at hospital discharge, and 2 weeks after surgery. Operationally, a VAS is usually a horizontal line, 100 mm in length, anchored by word descriptors at each end, such as no stress versus highest stress possible [37].Patients’ *self-reported pain* was measured using a VAS for pain measurement at enrollment (baseline), at admission for surgery, at hospital discharge, and 2 weeks after the surgery. The VAS for pain is a validated single-item scale that is anchored by “no pain” (score of 0) and “pain as bad as it could be” or “worst imaginable pain” (score of 100). The VAS presents a high internal consistency, as shown by a Cronbach α of 0.9117 [38].Patients’*Hospital Anxiety and Depression Scale* (HADS) scores were measured at admission for surgery, at hospital discharge, and 2 weeks after surgery. The HADS consists of 2 dimensions with 7 questions each, one representing the anxiety subscale and the other representing depression, with both psychopathological concepts of anxiety and depression being independent. Each item was rated on a 4-point frequency scale, ranging from 0 to 3. The internal consistency of the HADS, as measured by the Cronbach α coefficient, was found to be .78 for the anxiety subscale and .86 for the depression subscale, indicating satisfactory reliability [39].

To assess the secondary outcome variables, the following questionnaires will be used after each standard care visit and will be administered paper and pencil:

Patients’ *health-related quality of life* (HRQoL) was measured using the EQ-5D-3L questionnaire at enrollment, admission for surgery, and at clinical discharge. EQ-5D-3L measures HRQoL across 5 dimensions: mobility, self-care, usual activities, pain or discomfort, and anxiety or depression [40]. These dimensions are scored as “no problems,” “moderate problems,” or “severe problems.”Patients’ *emotional status* was measured at enrollment (baseline), at admission for surgery, at hospital discharge, and 2 weeks after surgery using the Positive and Negative Affect Schedule (PANAS). The PANAS is represented by 10-items evaluating positive and negative affectivity in terms of descriptive adjectives (eg, active or upset). Responses ranged from 1 (“never”) to 5 (“very much”). Cronbach α indicated excellent internal consistency for both factors (.90 and .91, respectively) [41].Patients’ and caregivers’ * mental well-being* was measured at enrollment and 2 weeks after the surgery using the “Short Warwick Edinburgh Mental Well-Being Scale.” This instrument specifically targeted positive mental functioning. The scale is composed of 7-items (eg, “I’ve been feeling useful”) with a 5-point response range from (“none of the time” to “all of the time”). The questionnaire has high internal consistency reliability, with a Cronbach α of .89 [42].Patients’ and caregivers’*self-efficacy* measured at enrollment and 2 weeks after surgery using the General Self-Efficacy in Short Form (GSE) questionnaire. Self-efficacy refers to the general perception of one’s capability to handle adversities. The GSE-SF is a 6-item scale wherein several self-descriptive sentences are scored from 1 (“not at all true”) to 4 (“exactly true”). The questionnaire presents high internal consistency reliability with a Cronbach α of .85 [43].Patients’ *activation status* was measured using a self-reported questionnaire, the Patient Activation Measure short form (PAM-13), at enrollment, admission for surgery, and 2 weeks after surgery. PAM-13 is an instrument that assesses patient knowledge, skills, and confidence in the management of chronic conditions [44]. Response options ranged from (1) strongly disagree to (4) strongly agree, and an additional “not applicable” option. The questionnaire presents high internal consistency reliability with a Cronbach α of .81.

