**Objective:**

This study aimed to explore the feasibility of a digital health intervention called the Adhera CARINAE Digital Health Program, designed to provide evidence-based, personalized stress- and anxiety-management methods enabled by a comprehensive digital ecosystem that incorporates wearable, mobile, and virtual reality technologies. The intervention program includes the use of advanced data-driven techniques for tailored patient education and lifestyle support.

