## Methods

### Overview

The Adhera CARINAE Digital Health Program will be tested in a multicenter trial, including 5 clinical settings across 3 European countries, and will use a stratified randomized controlled design including 30 intervention participants (6 per clinical site) and 30 control group participants (6 per clinical site; Multimedia Appendix 5). This study aimed to obtain objective answers to the following 2 research questions:

Is the designed protocol feasible for conducting a future definitive randomized controlled trial? Accordingly, to what extent does the program affect patients’ and caregivers’ stress, anxiety, and pain levels, and secondarily, well-being and overall quality of life, compared with patients receiving the standard of care only?What is the overall usability of the digital health solution based on the experience of patients, caregivers, and HCP?

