#### Research Question 2 (Usability Outcome Variables)

The usability of the intervention tools will be monitored during hospital stay and posthospitalization using well-validated and ad hoc metrics. The *System Usability Scale*, *Net Promoter Score*, and an ad hoc *usability questionnaire* will be administered to the intervention group patients and caregivers as well as the HCPs who are involved in the care management of the intervention group [45,46].

The System Usability Scale is a 10-item evaluation based on a 5-point Likert scale measuring the strength and agreement of usability [45].

The ad hoc *usability questionnaire* assessed 4 dimensions: (1) functionalities, (2) design, (3) manual and instruction for use, and (4) general usability on a Likert scale (1-10). Each dimension also contained open fields to which participants responded qualitatively.

Net Promoter Score is used to assess general satisfaction with the question, “How likely are you to recommend this service?” [46]. The response format ranged from –100 to +100. Specific satisfaction was measured using a Likert scale (0-100) on a single question (“Did the user like the CARINAE solution?”).

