### Data Analyses

The analyses will be conducted in Python 3.9.5 through the IDE PyCharm Community Edition 2021.2.1 Software and intention-to-treat principles. Descriptive statistics will be used to characterize the groups during the 4 visits. Furthermore, owing to the small sample size, Spearman correlations will be performed with all the variables to check, first, for potential associations between the variables and, second, differences between the intervention versus control groups. Further potential differences between these groups will be analyzed as follows:

Stress (VAS), pain (VAS), and mood state (PANAS-short form) will be subjected to a multivariate mixed analysis of variance (split-plot ANOVA) with “time” as a within-subject factor (ie, 4 time points) and “group” as a between-subject factor (intervention vs control).Patient activation (PAM-13) and self-efficacy (GSE-SF) will also be submitted to a multivariate mixed analysis of variance with “time” as a within-subject factor (Ie, 3 time points) and “group” as a between-subject factor (intervention vs control).Mental well-being (Short Warwick Edinburgh Mental Well-Being Scale) and HRQoL (EQ-5D-3L and EQ-5D-Y) will be analyzed using multivariate mixed analyses of covariance. As measurements of these 2 variables are based on a pre-post design, postmeasurements will be used as the dependent variable and premeasurements as covariates.

Finally, it is of interest to explore the effects as a function of different types of surgery. To this end, 2 different statistical approaches will be used:

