## Discussion

### Overview

The primary objective of the proposed study is to assess the feasibility of a digital health support program and its related technologies, that is, wearables, mobile apps, and VR for reducing perioperative stress. The results of this project will inform the development of best practices for patients’ stress relief during the perioperative process.

Several strategies and techniques have been proposed to manage preoperative stress and anxiety, which can be effective in supporting patients to cope with a wide range of stressful health situations. In current health care settings, however, it is not very common to provide patients with stress and anxiety relief support before a surgical procedure. The available VR apps focus only on providing informative content, neglecting the importance of patient empowerment with a more robust educational curriculum. This study will be among the first to evaluate the potential effectiveness of complete IVR technology for reducing perioperative stress.

This protocol describes a complete digital health solution that offers a unique combination of end points and the integration of knowledge derived from several domains, including stress and anxiety management, patient empowerment, communication with medical professionals, adaptation to illness, self-regulation, self-management, and adaptation to medical procedures.

This digital health solution allowed participants to receive constant feedback to improve their appraisal and coping skills in an entertaining and motivating manner. It focuses on patient empowerment through active participation in the process and is dynamically adapted according to operation type, patient preferences, needs, and medical history throughout the preclinical phase, admission, and discharge in a continuous and personalized manner. Simultaneously, it facilitates effective interactions between patients and HCPs through user-friendly and intelligent communication. It uses the spaced learning methodology to help patients understand and learn the diverse aspects of their surgical process, from presurgery requirements to recovery steps with stress management throughout the process and provides multichannel anxiety and stress-relief personalized content.

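### Feasibility is the declared primary objective, but the outcomes and analyses listed for research question 1 address only its second half, the effect on stress, anxiety and pain

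*Protocol article*

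**What the plan says.** **Objective.** The abstract states: "This study aimed to explore the feasibility of a digital health intervention called the Adhera CARINAE Digital Health Program". The Discussion (Overview) is firmer: "The primary objective of the proposed study is to assess the feasibility of a digital health support program and its related technologies".

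**Research question 1** (Methods, Overview) has two parts. The first is "Is the designed protocol feasible for conducting a future definitive randomized controlled trial". The second, within the same question, is "to what extent does the program affect patients’ and caregivers’ stress, anxiety, and pain levels", in comparison with standard care.

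**Outcomes assigned to question 1** (section Research Question 1): "Stress, anxiety, and pain represent the primary outcome variables that will be measured using paper-and-pencil questionnaires". Then: "The secondary outcome variables were overall quality of life, emotional status, mental well-being, self-efficacy perception, and patient activation during and after hospital stay". Table 1 gives the same division. Its primary rows are VAS stress (patients and caregivers), VAS pain and the HADS.

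**Outcomes assigned to question 2** (section Research Question 2): "The usability of the intervention tools will be monitored during hospital stay and posthospitalization using well-validated and ad hoc metrics". These are the System Usability Scale, the Net Promoter Score and ad hoc usability and satisfaction items.

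**Analysis.** Data Analyses gives group descriptives over the four visits and Spearman correlations, and continues: "Further potential differences between these groups will be analyzed as follows". Mixed ANOVA and ANCOVA models, analyses by surgery type and linear mixed models follow.

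**Withdrawals.** Withdrawal From the Study says that the information of a participant who withdraws is left out of the analysis.

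**The concern.** A trial whose primary objective is feasibility should have a primary outcome that can show the trial to be feasible or not. Here the outcomes labelled primary are clinical effect scales. None of the outcomes listed under question 1 says whether patients approached agree to take part, stay to the fourth visit, complete questionnaires that take 15 to 45 minutes per visit, or use the app and headset.

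At stake is what the definitive trial can take from this one. Its planners will need consent, retention and completeness rates with their uncertainty, and SDs of the clinical scales. The plan as written yields tests of group differences and does not commit to any of those rates. The rule on withdrawals makes this worse, because it takes out of the analysis the people whose loss a retention rate should count.

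**Working it through.** **1. Each part of the aim against the outcomes and analyses given for it**

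| Aim | Outcome listed | Analysis listed |
|---|---|---|
| Q1, first part: protocol feasible for a definitive trial | none | none |
| Q1, second part: effect on stress, anxiety, pain | VAS stress, VAS pain, HADS (primary) | group, time and interaction models |
| Q1, second part: well-being and quality of life | EQ-5D, PANAS, SWEMWBS, GSE-SF, PAM-13 (secondary) | same family of models |
| Q2: usability | SUS, NPS, ad hoc items | not itemised |

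The gap is in the first row only.

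**2. The sample size.** Sample Size says that a feasibility study needs no calculation. It then gives 60 (30 per group) for power 0.8, α .05 and effect size 1.20. Reading 1.20 as a standardised mean difference, two-sided (the section states neither the metric nor the sidedness):

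n per group = 2(1.960 + 0.842)² / 1.20² = 15.70 / 1.44 = 10.9, so 11. The exact t-test needs 11.94, so 12 per group and 24 in total.

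The stated 60 is not reproduced. This is a separate matter. Its bearing here is that 60 is justified by effect testing and not by the precision of any feasibility rate.

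**3. What 60 participants could say about feasibility.** The article gives no rates, so the proportions below are assumptions. Wilson 95% interval, z = 1.96:

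[p + z²/2n ± z√(p(1−p)/n + z²/4n²)] / (1 + z²/n)

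For 51/60, p = 0.85:
- Centre: (0.85 + 0.0320) / 1.0640 = 0.829
- Half-width: 1.96 × √(0.002125 + 0.000267) / 1.0640 = 0.090
- Interval: 0.739 to 0.919

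Other assumed rates, by the same formula:

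| Assumed rate | n = 60 | n = 30 (one arm) |
|---|---|---|
| 60% | 0.474 to 0.714 | 0.423 to 0.754 |
| 70% | 0.575 to 0.801 | 0.521 to 0.833 |
| 80% | 0.682 to 0.882 | 0.627 to 0.905 |
| 90% | 0.799 to 0.953 | 0.744 to 0.965 |

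**4. Effect of the withdrawal rule.** Suppose 9 of 60 withdraw and nobody else is lost. Retention is 51/60 = 85%. With the 9 removed it becomes 51/51 = 100% by construction.

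**5. Several primary scales.** The article names α = .05 only under Sample Size. If each of k primary scales were tested at .05 and the tests were independent, the chance of at least one false positive would be 1 − 0.95^k:
- k = 3 (stress, anxiety, pain): 1 − 0.857 = 14%
- k = 4 (caregiver stress counted separately): 1 − 0.815 = 19%
- k = 5 (HADS depression added, as in Table 1): 1 − 0.774 = 23%

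Positive correlation lowers these; with five scales correlated 0.5, simulation gives 18%.

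**The case against.** Four points can be made for the plan.

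**Question 1 also asks about effect.** This stands. The declared primary outcomes answer that part directly, so a reader who infers that the plan cannot answer question 1 at all goes too far. The unanswered part is the one that comes first and matches the declared primary objective.

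**Usability is a form of feasibility.** This stands in part. The abstract and Discussion speak of feasibility of the program, and usability and satisfaction ratings inform its acceptability. But the article places them under question 2, and they rate the tool. They do not show whether patients enrol, remain and complete the questionnaires.

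**A journal article condenses.** Progression criteria and flow summaries may be in the full protocol or SAP. The article also commits to CONSORT guidance for feasibility trials, and the flow figure and SPIRIT appendix are not visible here. That is a reason not to claim that no such data will be reported. It does not remove the mismatch: the article does list outcomes by research question, with instruments and visits, and it labels the effect scales as primary.

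**It is late to change.** Results says that recruitment is complete and analysis is under way. This stands, and it limits what can still be called prespecified.

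A reader might also infer that feasibility would be judged by p values, with a non-significant result read as infeasible. No section ties a feasibility or progression decision to any test. Nor is it settled that there are five primary scales. The outcome text names three constructs, and five is reached only by separating caregiver stress and adding depression from Table 1.

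**Conclusion.** The point holds in limited form. The outcomes labelled primary and secondary for question 1, and the analyses described, address the effect half of that question. The feasibility half, which is the declared primary objective, has no matching outcome or analysis in the article. This is a mismatch in what the article states, and not merely detail left to another document. The withdrawal rule adds to it by excluding the participants that a retention estimate must count.

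The size of the defect is not a number. The precision figures show only that the planned sample could support the missing estimates: half-widths of roughly 8 to 12 percentage points with all 60, and 11 to 17 in one arm, for assumed rates of 60% to 90%. The 14% to 23% range assumes independent tests at .05 on three to five scales. It is a reason to treat the clinical comparisons as estimates and does not describe how feasibility would be decided. No safety issue arises. The change should be made before the results are reported.

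**What to change.** For the feasibility part of question 1, name as primary outcomes:

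- the proportion consenting among patients approached, by site where records allow;
- retention at visit 4 by arm, with withdrawals counted as not retained;
- completeness of the primary questionnaires at each visit;
- app use in the intervention arm, and VR use if it was logged.

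Report each with a 95% CI and compare it with a progression value. Fix those values before these data are examined; where that is no longer possible, declare them post hoc. Amend the withdrawal rule so that a withdrawal is still counted in the retention figure, including when the participant's questionnaire data are removed on request.

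Present stress, pain and HADS anxiety as clinical outcomes, with between-group differences, 95% CIs and SDs for planning, and not as confirmatory efficacy tests. Keep usability under question 2 as evidence on acceptability of the tool.

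**Cost.** The work is mainly relabelling and simple proportions, provided that the records exist. The article describes prescreening and invitation but no screening log, and it mentions app interaction data but no VR logging, so availability must be checked first. The trial gives up any confirmatory efficacy claim. The change must be disclosed in the report as made after recruitment had ended.

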#### Research Question 2 (Usability Outcome Variables)

The usability of the intervention tools will be monitored during hospital stay and posthospitalization using well-validated and ad hoc metrics. The *System Usability Scale*, *Net Promoter Score*, and an ad hoc *usability questionnaire* will be administered to the intervention group patients and caregivers as well as the HCPs who are involved in the care management of the intervention group [45,46].

The System Usability Scale is a 10-item evaluation based on a 5-point Likert scale measuring the strength and agreement of usability [45].

The ad hoc *usability questionnaire* assessed 4 dimensions: (1) functionalities, (2) design, (3) manual and instruction for use, and (4) general usability on a Likert scale (1-10). Each dimension also contained open fields to which participants responded qualitatively.

Net Promoter Score is used to assess general satisfaction with the question, “How likely are you to recommend this service?” [46]. The response format ranged from –100 to +100. Specific satisfaction was measured using a Likert scale (0-100) on a single question (“Did the user like the CARINAE solution?”).

#### Independent Variable

The independent variable in this study was the type of intervention. This variable is allocated to 2 levels: control and intervention.

#### Confounding Variables

Patient age, sex, surgery type, medication use, length of hospital stay, and health outcomes, such as postoperative complications, reoperation, mortality, and groups in which the patients were involved during the intervention, will be used as confounding variables.

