## Introduction

### Background

Patients undergoing surgical operations exhibit symptoms of severe stress, anxiety, and fear as common physiological and psychological reactions to potentially threatening situations associated with surgeries [1,2]. Family caregivers are expected to assume a complex caregiving role for these patients and are therefore confronted with emotional distress and physical decline as well [3].

Surgeons and health care professionals (HCPs) use a variety of stress-coping strategies, as stressors that affect surgical performance and contribute to complications [4]. Psychological support and patient education have proven to be very effective in reducing this stress and anxiety [5,6]. Provision of information about their surgery constitutes an essential part of the preoperative experience both in patients and their caregivers because it helps decrease anxiety levels as well as surgical complications [7,8]. Patient empowerment improves self-care management, encourages patients to take an active role in managing their diseases, and expands outcomes such as satisfaction, cost, health status, and function [9]. Addressing caregiver strain is also an important aspect of care for pediatric patients [10] and those with special health care needs [11].

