**Figure 2 figure2:**
[figure not shown]
The Adhera Health CARINAE Digital Program mobile app.

As part of the integration with the existing clinical workflow, the mobile solution provides a *communication module* where patients can chat with their health care team through an asynchronous chat.

One of the key elements of a mobile solution is *personalization*, which maximizes patient engagement. A core element of the personalization strategy is the use of the Adhera HRS, which provides personalized messages to patients based on behavioral change models such as the I-Change model [26]. These messages are tips and pieces of advice about how to adopt healthy behaviors such as quitting smoking before and after surgery to improve recovery length. Patients are guided to adhere to healthier habits and reduce their stress and anxiety levels before and after surgery.

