#### Control Group

The control group will not use the digital solution and will receive standard care consisting of visits to the health care provider. Patients in the control group were provided with instructions on diet and healthy lifestyle habits; however, in current health care settings, it is not very common to provide patients with stress and anxiety perioperative relief support. Assessments of the control group will be performed during the following visits:

The initial visit on which the HCP communicates to the patient the need for surgery (2-4 weeks before surgery);Hospital admission (1-3 days before surgery);Hospital discharge (approximately 1 week after surgery);Remote follow-up 14 days after the surgery.

Following each visit, several questionnaires will be administered to patients with a duration ranging from 15 to 45 minutes according to the visit (Table 1).

**Table 1 table1:** Key parameters and measurements: baseline is 2-4 weeks before surgery, (hospital) admission is 1-3 days before surgery, (hospital) discharge is 1 week after surgery, and postoperative is 2 weeks after surgery.

Variables		Participants	Measurements	Baseline	Admission	Discharge	Postoperative

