**Covariates**							
	Demographics	Patients	Self-report assessment questionnaire	Yes	No	No	No
	Clinical data	HCPs	HCP report	Yes	Yes	Yes	Yes
	Length of hospital stay	Patients	HCP report	No	Yes	Yes	No

^a^VAS: visual analogue scale.

^b^HADS: Hospital Anxiety and Depression Scale.

^c^HRQoL: health-related quality of life.

^d^PANAS: Positive and Negative Affect Schedule.

^e^SWEMWBS: Short Warwick Edinburgh Mental Well-Being Scale.

^f^GSE-SF: General Self-Efficacy-Short Form.

^g^PAM-13: Patient Activation Measure short form.

^h^HCP: health care professional.

^i^SUS: Stem Usability Scale.

^j^NPS: Net Promoter Score.

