#### Experimental (Intervention) Group

The experimental group will receive a digital health solution during the first visit, and training on how to use this tool will be provided. Patients will take the digital health solution home with them and can use it as often as they like. The experimental group, after each 1 of the 4 standard care visits, will complete the same questionnaires as the control group.

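### Length of stay, complications, reoperation and death arise after randomisation and cannot be confounders; the confounder list contradicts the stated models and should be cut to pre-allocation variables

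*Protocol article*

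**What the plan says.** The Confounding Variables section names age, sex, surgery type and medication use, and continues with "length of hospital stay, and health outcomes, such as postoperative complications, reoperation, mortality, and groups in which the patients were involved during the intervention". It closes with the unqualified statement that these "will be used as confounding variables". Table 1 has a row "Length of hospital stay" under Covariates, marked as recorded at admission and discharge but not at baseline.

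The Independent Variable section defines the exposure as type of intervention: "This variable is allocated to 2 levels: control and intervention".

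Data Analyses commits to intention-to-treat principles and describes the models:
- mixed analyses of variance with time and group;
- analyses of covariance with the pre-measurement as covariate;
- separate analyses by surgery type;
- a linear mixed model with time, group and their interaction as fixed factors, subject and surgery as random factors, and age or sex as optional covariates.

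**The concern.** A confounder is a cause of the outcome that is also associated with treatment without being a result of it. Randomisation removes such associations except by chance, and chance imbalance concerns only variables already fixed at allocation. A variable that arises later may be an effect of treatment. Conditioning on it removes whatever part of the effect passes through it. If it shares an unmeasured cause with the outcome, such as frailty, conditioning also creates an association between arm and outcome that treatment did not produce.

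What is at stake is the second part of research question 1: how far the programme changes stress, anxiety and pain compared with standard care. An estimate adjusted for these variables would answer a different question from the intention-to-treat one.

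**Working it through.** **1. Timing.** The Experimental (Intervention) Group section says: "The experimental group will receive a digital health solution during the first visit". The Control Group section places that visit 2-4 weeks before surgery, admission 1-3 days before surgery, discharge about 1 week after surgery, and the last assessment 14 days after surgery. Age, sex and surgery type are fixed before allocation. Length of stay, postoperative complications, reoperation and death are not. The timing of medication use is not stated.

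**2. Possible effect of treatment.** On giving patients information about their surgery, the Background says "it helps decrease anxiety levels as well as surgical complications". The mobile app section describes messages on healthy behaviours, "such as quitting smoking before and after surgery to improve recovery length". The rationale thus puts complications and recovery downstream of the programme.

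**3. Time points.** The admission assessment precedes surgery. Adjusting it for complications, reoperation or death would condition on later events. The abstract says that stress and anxiety can increase complications, so these events may even be consequences of the outcome being analysed. Mortality also fails as a covariate for later self-reports, because a patient who has died provides none.

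**4. The list against the models.**

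| Variable | Confounding Variables | Models in Data Analyses |
|---|---|---|
| Age, sex | listed | optional in the mixed model |
| Surgery type | listed | random factor; also separate analyses |
| Medication use | listed | not entered |
| Length of stay | listed (also Table 1) | not entered |
| Complications, reoperation, mortality | listed | not entered |
| Groups | listed | the effect of interest, if the arm is meant |
| Pre-measurement | not listed | covariate for well-being and quality of life |

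**5. Size.** The plan gives no figure on this point, so there is none to reproduce. The following is an illustration; every path strength is an assumption. Let T be the arm, U an unmeasured cause, M the post-allocation variable and Y the outcome, with

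M = aT + uU + noise, Y = cT + bM + uU + noise,

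where noise is scaled so that Var(M given T) = 1 and the part of Y not due to T or M has variance 1. Then:
- total effect = c + ab;
- slope of Y on M within arm = b + u²;
- effect adjusted for M = (c + ab) − a(b + u²) = c − au².

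| Case | a, b, u, c | Total, formula | Adjusted, formula | Simulated: unadjusted, adjusted | Rejection rate: unadjusted, adjusted |
|---|---|---|---|---|---|
| Half the effect acts through M | −0.5, 0.5, 0, −0.25 | −0.25 − 0.25 = −0.50 | −0.25 | −0.505, −0.251 | 0.40, 0.16 |
| All of it acts through M | −1, 0.5, 0, 0 | −0.50 | 0 | −0.501, 0.008 | 0.39, 0.05 |
| No effect on Y; M affected; shared cause | −0.8, 0, 0.6, 0 | 0 | 0.8 × 0.36 = 0.288 | −0.003, 0.282 | 0.05, 0.18 |
| Treatment does not affect M | 0, 0.5, 0.5, −0.5 | −0.50 | −0.50 | −0.504, −0.499 | 0.34, 0.49 |

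The simulation used 60 patients allocated 1:1, 4,000 runs and two-sided tests at 0.05. The distortion is total minus adjusted, a(b + u²). It is zero when a = 0, that is, when treatment does not affect the adjusted variable.

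**The case against.** The strongest reply is that no stated model does what the list says. Data Analyses is the operative section, and it uses time, group, pre-measurement and surgery, with age or sex optional. This stands, and it limits the point. A reader might infer that the trial's treatment effect will be biased or removed; the documents do not support that, because no described analysis enters length of stay, complications, reoperation or mortality. It does not dispose of the point, however. The commitment in Confounding Variables is unqualified, Table 1 repeats it for length of stay, and nothing in Data Analyses withdraws it.

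A second reply is that the causal path is thin. The app passage concerns smoking cessation and recovery, not hospital stay as such; the Background statement is general; and no figure is given for any effect of the programme on these variables. This also stands. Bias arises only if treatment affects the adjusted variable, so the illustrative figures must not be read as estimates for this trial. The variables remain ineligible as confounders on timing alone.

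A reader might also infer that listing the groups as a confounder makes the treatment effect inestimable or takes it away. Entering the arm twice would indeed give a rank-deficient design (rank 2 for 3 columns: intercept, group, group), but no stated model does so, and calling a term a nuisance does not change its coefficient. The phrase is also loose and could mean some other grouping. If it means the arm, the exposure has been mislabelled; no bias is shown.

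Finally, this is a feasibility study. That lowers the stakes, but research question 1 still asks for the comparative effect.

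**Conclusion.** The point holds as an error in the stated adjustment set and a contradiction between sections. Length of stay, complications, reoperation and mortality arise after allocation, cannot confound the randomised comparison, and are in part outcomes that the protocol's rationale expects the programme to improve. An analysis that followed the list would depart from the total intention-to-treat effect and could be biased in either direction.

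The size cannot be derived from the documents. In the illustration the adjusted estimate kept all, half or none of a true effect of 0.50, or showed 0.28 where there was none, depending wholly on the assumed paths. Age, sex and surgery type are legitimate covariates. Medication use is legitimate only if recorded before allocation. The entry on groups is a wording matter.

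**What to change.** - In Confounding Variables, limit adjustment to variables fixed before allocation: age, sex, surgery type, the baseline value of the outcome where it is measured, and medication use only if recorded before allocation. For the Hospital Anxiety and Depression Scale, Table 1 shows a baseline measurement but the Outcome Variables text does not, so this must be settled first.
- Remove length of stay, complications, reoperation and mortality from the list, and report them descriptively by arm.
- Take length of stay out of the Covariates block of Table 1, and align both places with Data Analyses so that one adjustment set applies throughout.
- Delete the entry on groups if it means the study arm; otherwise say which grouping is meant and when it is fixed.

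The cost is wording only; no additional data are needed. The Results section says that recruitment is complete and the primary impact analysis is ongoing, so the change should be made and dated before any adjusted result is reported.
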